Those PwMS who are followed primarily by a family physician, outside of a neurologist, can be referred by their family physician directly to the NP via the established tertiary MS clinic fax system. These referrals will be screened by the NP and one of the researchers (PS, a MS specialist neurologist). Those who meet the eligibility inclusion criteria will be invited to take part in the study. If the patient consents to the study, they will be randomized to either the intervention or control arm as per this study protocol. If the patient is randomized to the control arm, the family physician will be informed that the referral for the NP would be scheduled for after study conclusion: 6 months after the date of referral. Family physicians will be given the additional opportunity of referring the patient to a community neurologist or a NP outside of the study if they feel that the patient cannot wait 6 months for MS specialized care. If the family physician opts for more urgent patient assessment, these patients will be excluded from being involved in the study.

Caregivers will be approached and invited to participate in the study, if the PwMS indicates a caregiver and contact information through their participant consent process. At the end of the informed consent, the PwMS will be asked whether they have a caregiver (with our definition for this study provided). If the participant answers ‘yes they have a caregiver’, they will be invited to provide the caregivers’ name, email address, and/or physical address. A separate informed consent will then be sent to the caregiver by email or by mail, outlining their involvement in the study and seeking their informed consent. Date of first enrolment was July 28, 2017, and recruitment was completed as of March 29, 2019.

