### Control arm (usual care arm)

PwMS who are randomized to the usual care arm (community neurologist or family physician and registered nurses) will be contacted by the NP to be scheduled for an NP appointment at 6 months after study conclusion. Thus, every PwMS is given the opportunity to access NP care after their involvement in the study has concluded. During the 6-month period, patients randomized to the control group will receive usual care from community neurologists or family physicians and MS registered nurses. The care will be delivered according to standard practices, and follow-up visits will be conducted according to the various clinical practices of the neurologists’ or family physicians’ clinics. For those in the usual care arm, the EPICORE Centre’s research team will contact the participant +/− caregiver about the completion of questionnaires at the appropriate timepoints. The participant diary will be collected by the NP when the participant in the usual care arm has finished the study and is offered a follow-up visit with the NP outside of the study. If family physicians wish to have more urgent patient assessments, they will be offered the additional opportunity of referring the patient to a community neurologist or a NP outside of the study if they feel that the patient cannot wait 6 months for MS specialized care; these patients will also be excluded from being involved in the study.

Participants are able to initiate contact with their usual community neurologist and/or family physician in either arm of the study, throughout the study as they need. Participants will continue to be followed by their family physicians and regular community neurologists during the study, in either arm. For those in the NP-led care arm, they will receive additional care by the NP during the 6 months of the study duration.

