A longer-term follow-up will be conducted at 12 months to evaluate the long-term differences of the 6-month intervention in change of the patient-reported outcome measures (HADS, MFIS, EQ5D, and CAREQOL-MS). By then, all participants would have seen the NP, and the goal of the late follow-up would be to see if there was (1) long-term impact of the 6-month NP intervention (from those in the original intervention group), and (2) to check the larger patient number impact of the NP intervention upon those within the control group.

If participants score very low or severe on their scales around anxiety, depression, fatigue, quality of life, and/or their caregivers score as very low on their questionnaire, their community neurologist and/or family physician will be contacted to see the participant on an urgent basis.

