### Validity and reliability

The questionnaires used in the study (EQ5D, HADS, MFIS, and CAREQOL-MS) have been tested for validity and reliability in studies involving PwMS. Three papers report total HADS scores in PwMS and were considered in the study design of this study [74–76]. The EQ5D quality of life measure is commonly used in the MS population [23], and the MFIS is a standard measurement of fatigue in PwMS [82, 87]. The CAREQOL-MS, a caregiver quality of life survey for those caring for PwMS is also commonly used in this patient population [83, 88]. Satisfaction with healthcare provider care will be measured by the overall mean score of the CSQ completed at the 6-month follow-up visit. The CSQ is a self-administered tool with 18 questions; it measures 3 factors of the healthcare provider interaction: (1) professional aspects; (2) depth of patient relationship with provider; and (3) perceived length of consultation. The higher the score indicates a higher level of patient satisfaction [73, 84].

To reduce possible biases in the study, we will use objective measures to examine the effects of NP-led care in comparison to standard care. It is important that all participants will be offered an opportunity to see a NP either within 4 weeks for the intervention arm or at 6 months for the control arm. Thus, those participants randomized to the control arm will be provided with an appointment with the NP at 6 months. Then, 12-month follow-up of all participants will be conducted, to see if the timing of intervention makes a difference over the long term.

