### Dissemination, ancillary, and post-trial care

The longitudinal care for participants will continue throughout the study by their community neurologists and/or family physicians, in addition to the NP care in the intervention arm, as an add-on member of the care team, and described previously. Those in the control arm of ‘usual care’ will have an appointment with the NP at the end of the study, to receive the ‘add-on’ care from the NP for the 6 months after study completion, to ensure that every participant has access to seeing the NP. The results of this study will be shared with Alberta Health Services in consideration of their continuing to fund the position for supporting community neurologists in an outreach model going forward after the study. The hope is that the NP will continue in the outreach model established during the study. We are planning to have the NP position continue to operate within a 6-month intervention period, followed by referral of the PwMS back to their community neurologists and/or family physicians. This will enable the NP to take new patients over time, and not saturate the NP practice with long-term follow-ups. PwMS will always have the option of being re-referred back to the NP for another 6-month period.

This randomized control trial will be published once data analysis has been completed and all investigators will be invited to contribute to the manuscript. A copy of the publication and findings will be provided to the participants. At this time, there are no plans or arrangements for data sharing. We plan to disseminate the results at the European Committee for Treatment and Research in Multiple Sclerosis (ECTRIMS) conference, present to the Alberta MS Research Network, and to publish outcomes of the study in a peer-reviewed journal.

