## Limitations

There are study limitations inherent within the process of inviting PwMS to participate in a study looking at alternate ways of delivering care through a NP. This study preferentially selects for individuals who are open to having an NP provide care to them. Additionally, participants are not blinded as to whether they will be in the intervention arm vs the control arm. We will try to address that bias by offering NP visits to every participant in the study—either within 4 to 6 weeks for the intervention arm, or for those in the control arm at 6 months once the study concludes. An additional limitation might be that the NP may initiate appointments and/or phone calls with participants in the intervention arm beyond the three visits outlined in the study protocol where deemed clinically appropriate. We have limited participants to those who speak English and who can attend visits with the NP. This may limit the generalizability of the results with those who live in more rural areas, and those who primarily speak different languages. Finally, we will be relying on participants’ self-reported data to complete patient diaries to record their outpatient interactions with the healthcare system (e.g. family physician and neurologist visits and phone calls) and to complete the questionnaires which could be susceptible to subjective bias. We cannot control all of the healthcare providers that will be accessed by participants in either arm but will keep track of that information through the completion of patient diaries, and the search of Netcare, provincial clinical data records. As well, referral to the appropriate providers for support (i.e. psychologist) is part of the intervention itself when initiated by the NP to improve participants’ depression, anxiety, and quality of life. Since this is being tracked in our study, we may see that part of the NP’s impact upon the participants in the intervention arm is to correctly connect participants with the appropriate support services. Finally, ‘usual care’ amongst similar NP studies and amongst practitioners does vary, a limitation of any study trying to assess interventions above and beyond norms of clinical practice.

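### The control arm's NP appointment is dated from inconsistent anchors, and for family-physician referrals one of them can fall before the 6-month questionnaires

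*Protocol article*

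**What the plan says.** The protocol article places the control arm's NP appointment as follows.

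- Recruitment, for patients followed by a family physician without a neurologist: "the referral for the NP would be scheduled for after study conclusion: 6 months after the date of referral".
- Control arm (usual care arm): controls "will be contacted by the NP to be scheduled for an NP appointment at 6 months after study conclusion". The next sentence adds that "every PwMS is given the opportunity to access NP care after their involvement in the study has concluded".
- Validity and reliability: "those participants randomized to the control arm will be provided with an appointment with the NP at 6 months".
- Dissemination, ancillary, and post-trial care: controls "will have an appointment with the NP at the end of the study".
- Limitations: "for those in the control arm at 6 months once the study concludes".
- Outcomes, on the 12-month follow-up: "By then, all participants would have seen the NP".

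Data collection schedules questionnaires at baseline, 3, 6 and 12 months and invites participants to complete them once they have consented. Table 1 places the baseline questionnaires after allocation. The primary outcome is the change in HADS-D and HADS-A at 3 months. The 6-month secondary outcomes are HADS, EQ5D, MFIS, CAREQOL-MS and the CSQ.

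**The concern.** A between-arm comparison at 6 months needs a control arm that has not yet received the intervention. That depends on the order of two events in each control: the first NP contact and the 6-month questionnaires. The article uses three anchors for the first event (referral date, study conclusion, month 6) and does not name the day from which the questionnaires are counted.

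The Recruitment sentence is the sharpest case, because it treats the end of the study and six months from referral as the same date. In the family-physician route, referral is followed by screening, invitation, consent, randomisation and baseline, so the two dates differ by whatever time those steps take. If clinic staff book from the calendar rule, a control can see the NP first and report 6-month outcomes afterwards. The 6-month contrast would then be pulled toward no difference.

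A second consequence concerns month 12. If the Control arm wording is taken word for word, controls are first seen at about the time of the 12-month questionnaires. The stated purpose of that follow-up assumes they have already been seen.

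**Working it through.** No figure in the article depends on this point, so there is nothing of the plan's own to reproduce. The check is timeline arithmetic.

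Inputs:
- Referral is week 0. Six months is taken as 26.09 weeks and three months as half of that, 13.05 weeks.
- L is the lag in weeks from referral to baseline. The article does not give it, so it is an assumption, shown over a range. The nearest guide is the section on the intervention arm, which books the first NP appointment within 4 to 6 weeks of referral. The Abstract describes an NP assessment at a baseline visit, so L would be 4 to 6 if the baseline questionnaires coincide with that visit.
- The questionnaires are assumed to be counted from baseline.

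Formulas:
- NP visit under the referral anchor = 26.09
- 3-month questionnaire = L + 13.05
- 6-month questionnaire = L + 26.09
- Visit ahead of the 6-month questionnaire by (L + 26.09) − 26.09 = L

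| L (assumed) | NP visit, referral anchor | 3-month questionnaire | 6-month questionnaire | Visit ahead of 6-month questionnaire by |
|---|---|---|---|---|
| 0 | 26.1 | 13.0 | 26.1 | 0 |
| 2 | 26.1 | 15.0 | 28.1 | 2 |
| 4 | 26.1 | 17.0 | 30.1 | 4 |
| 6 | 26.1 | 19.0 | 32.1 | 6 |
| 13 | 26.1 | 26.0 | 39.1 | 13 |

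All entries are weeks from referral. The two halves of the Recruitment sentence agree only at L = 0. The 3-month primary questionnaire would come after the NP visit only if L exceeded about 13 weeks.

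Under the wording in Validity and reliability, Dissemination and Limitations, the visit falls at or after L + 26.09, so at or after the 6-month questionnaire. Under the word-for-word reading of Control arm, the visit is at (L + 26.09) + 26.09 = L + 52.18. That is 26.09 weeks after the 6-month questionnaire and level with the 12-month one, which does not fit the statement in Outcomes.

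**The case against.** The strongest reply is that the intended order is clear. The Recruitment sentence itself says the appointment follows the study, and Control arm, Dissemination and Limitations all place NP access after the study ends. This stands: the article contradicts itself on a date, but it does not plan to treat controls before the outcome. The statements of intent do not settle the matter, though, because the date given alongside one of them does not deliver it once there is any lag.

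A reader might infer several stronger things that the article does not support.

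- *That the whole control arm is booked before its 6-month questionnaires.* The referral anchor is written only for family-physician referrals. Their share is not stated, and the setting and feasibility sections centre on seven neurologists' practices.
- *That there are three irreconcilable dates and that the 12-month statement is false.* The Control arm phrase can be read as month 6, following study conclusion. The same section describes the alternative route as being for patients who could not wait six months, which favours that reading.
- *That controls fill in the CSQ at their first NP consultation.* Validity and reliability does refer to the "overall mean score of the CSQ completed at the 6-month follow-up visit", and usual care has no fixed visit then. But the coordinating centre sends surveys directly to participants and chases completion in the control arm, so the phrase is more likely loose wording.
- *That the 6-month effect shrinks by a calculable fraction.* That needs the share of controls seen early and the share of the NP effect gained from one early consultation. The article gives neither, and the 1.5-point difference in the sample size section is a planning value for the score comparison, not an estimate of the 6-month effect.

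**Conclusion.** The point holds as an inconsistency of dates with a limited statistical consequence. For family-physician-referred controls, the referral-based date precedes the 6-month questionnaires by exactly the referral-to-baseline lag. That lag is unknown, and is 4 to 6 weeks on the one assumption the article suggests. The conclusion rests on two conditions: the questionnaires are counted from baseline, and the referral date was in fact used for booking. Where both are true, the 6-month secondary comparisons are diluted to an extent that cannot be sized from the document. The primary 3-month comparison is not affected at plausible lags. The 12-month difficulty arises only on the word-for-word reading of Control arm.

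**What to change.** Reconcile Recruitment, Control arm, Outcomes, Validity and reliability, Dissemination and Limitations to a single statement of when controls are seen. Give one time zero for visits and questionnaires in both arms, and state explicitly whether the control NP visit comes before or after the 6-month questionnaires. Which schedule applies is for the investigators to say.

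Trial status reports that the last 6-month visit took place in November 2020 and that final analysis was still to come, so new wording cannot alter those appointments, but the analysis can still take account of them. Retrieve each control's date of first NP contact and flag any 6-month response dated after it. Report the flagged number, and add a sensitivity analysis of the 6-month outcomes that leaves those responses out without refilling them by the plan's last-value rule. Keep all randomised participants in the main comparison, since exclusion after randomisation can itself introduce bias.

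The cost is a wording correction, one extra date to retrieve per control and one extra analysis.

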### Intervention arm (NP-led care arm)

Participants randomized to the intervention group will be contacted by the NP to be scheduled for an appointment with the NP within 4 to 6 weeks from the date of the referral. The NP consultation will include patient history, physical examination, symptomatic management strategies as appropriate (e.g. bladder and bowel management strategies, fatigue management, depression, anxiety, spasticity), discussion of mental and physical health resources for symptomatic treatment, support, physical and mental health resources to optimize functioning (e.g. home care or physical/occupational therapy referral), and quality of life interventions. The NP will follow up with the patient either in person, by phone, or by videoconferencing at 3 months, at 6 months, and again at 12 months. The NP will be accessing the electronic medical record offered by Alberta Health Services [85] to maintain charting consistency in diagnostic testing, appointments, and communications [85]. During the visits, the NP will check the completion of study questionnaires at the appropriate timepoints, and ask the participant +/− caregiver about the completion of questionnaires. If the NP feels that he/she needs help in managing a participant, he/she will refer the participant back to the community neurologist and/or family physician in charge of the participant at any time throughout the study. As mentioned above, the NP will be sending summaries of visits to the neurologists and family physicians and may ask questions of the community neurologists as to their preferences in treatment approaches as needed (e.g. disease-modifying therapies, treatment of relapses with steroids) in individual situations. This fits within the multidisciplinary model of MS care, seen in MS clinics [11].

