### Preliminary screening

Prior to conducting statistical analysis, preliminary screening will be conducted using SAS 9.4 software (SAS Institute Inc., Cary, NC, USA) to ensure that all the enrolled patients meet the eligibility inclusion and exclusion criteria and confirm the participants provide informed consent.

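### Among family-physician referrals, control-arm participants can be excluded after randomisation on perceived need by a physician who knows the allocation; the NP arm has no matching exclusion

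*Protocol article*

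**What the plan says.** The protocol article, under Recruitment, gives the sequence for patients followed primarily by a family physician and not by a neurologist:

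1. Consent leads directly to randomisation: "If the patient consents to the study, they will be randomized to either the intervention or control arm as per this study protocol".
2. What follows depends on the arm: "If the patient is randomized to the control arm, the family physician will be informed that the referral for the NP would be scheduled". The date given is 6 months from referral, once the study has ended.
3. The physician may then refer the patient to a community neurologist or to an NP outside the study "if they feel that the patient cannot wait 6 months for MS specialized care".
4. The consequence is stated: "If the family physician opts for more urgent patient assessment, these patients will be excluded from being involved in the study".

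The section on the control arm repeats the offer and the consequence: "these patients will also be excluded from being involved in the study".

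In the section on the intervention arm, an NP who needs help with a participant has a referral route too: "he/she will refer the participant back to the community neurologist and/or family physician in charge of the participant at any time throughout the study". No exclusion is attached to it.

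The Drop-out criteria list non-response to three contacts and the participant's own wish to leave. They do not list a physician's decision. Under Statistical analysis, the primary test is an independent t-test on change in HADS-D and HADS-A from baseline to 3 months, with the last observation carried forward. Blinding of providers and patients is said to be impossible.

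**The concern.** An unadjusted t-test on change relies on randomisation to make the two arms alike apart from treatment. That holds only if the people compared are those who were randomised, or if losses are unrelated to outcome. Here the exit opens after allocation, is offered in one arm only, and turns on an allocation-aware physician's view of urgency. Perceived urgency is plausibly related to current distress or to its likely course, which is what HADS measures. The patients in the NP arm who would have been judged equally urgent stay in.

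At stake is the primary comparison for this recruitment route. Neither the inflation to 220 nor a blinded statistician repairs a selective loss from one arm.

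The rule also sits awkwardly with the comparator. Usual care is defined as care by a community neurologist and/or family physician. A control referred to a community neurologist, one of the two exits offered, would be excluded for receiving care of the kind the control arm is meant to represent.

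**Working it through.** **Could the exclusion be read as pre-randomisation?** The physician is informed only on the condition "If the patient is randomized to the control arm, the family physician will be informed", so allocation has already happened. The repetition under the control-arm heading points the same way.

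**Inputs from the protocol** (Sample size and power analysis): 100 per group, difference 1.5 points, 80% power, two-sided alpha 0.05. No SD is printed.

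**Implied SD.** The stated sample size cannot be reproduced without an SD, so I solved for it.
- Normal approximation: SD = 1.5 / [(1.960 + 0.842) × √(2/100)] = 3.79.
- t distribution: 3.77.

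I use 3.77 for the first illustration and 3.78 for the second, which returns 100 per group.

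**Assumed inputs** (none is in the protocol): the fraction of controls excluded, how strongly exclusion tracks HADS, and the correlation ρ between baseline and 3-month scores (0.5 to 0.7).

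**Illustration A: selection on high baseline scores.** If the top fraction p of controls is removed, the baseline mean of the remainder falls by SD × φ(z) / (1 − p). The bias in mean change is (1 − ρ) times that shift.

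| p (of all controls) | φ(z) | Shift in mean | Bias, ρ = 0.7 | Bias, ρ = 0.5 | Share of 1.5 |
|---|---|---|---|---|---|
| 5% | 0.103 | 0.41 | 0.12 | 0.20 | 8–14% |
| 10% | 0.175 | 0.74 | 0.22 | 0.37 | 15–25% |
| 20% | 0.280 | 1.32 | 0.40 | 0.66 | 26–44% |

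This is a ceiling for each p, because the removed patients are taken to be exactly the highest scorers.

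A milder case: if 20% of controls come through family physicians and 20% of those are excluded, p = 0.20 × 0.20 = 4%. The shift is 3.77 × 0.0862 / 0.96 = 0.34.
- Perfect selection on HADS gives a bias of 0.10 to 0.17 points.
- If exclusion correlates only 0.3 with HADS, the bias is 0.03 to 0.05 points, or 2–3% of the target.

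**Illustration B: selection on course.** If a fraction f of controls is removed and their mean change is D points worse than that of the remaining controls, the difference between arms shifts by f × D. Normal approximation, SD 3.78, 100 in the NP arm and 100(1 − f) in control:

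| f | D | Bias | Type I error if no true effect | Power if the true effect is 1.5 |
|---|---|---|---|---|
| 5% | 2 | 0.10 | 5.4% | 73% |
| 10% | 3 | 0.30 | 8.5% | 59% |
| 20% | 3 | 0.60 | 18.5% | 35% |
| 20% | 0 | 0 | 5.0% | 75% |

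The last row shows that removal unrelated to outcome costs some power but causes no bias.

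**Direction.** In A, removing high scorers takes regression to the mean out of the control arm only, which favours the NP. In B, removing controls who would have worsened flatters the control arm and hides benefit. The protocol does not say which would dominate.

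**The case against.** The strongest reply is about scope. The rule reaches only patients referred by family physicians. The trial is set in seven neurologists' offices, its feasibility rests on those practices' more than 2000 patients, and the neurologist recruitment route has no such exit. Losing 20% of all controls would require at least 20% of them to have come through family physicians and, at that minimum, every one of those to have been excluded. The trigger is also the physician's view of whether the patient can wait, not a HADS score. All of this stands, and it is why the upper figures are a worst case and not an expected size.

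Second, the text excludes patients from involvement in the study and does not mention the analysis set. Analysis populations may be defined in an analysis plan that is not shown, and a control with only a baseline score might be kept by carrying that score forward. This stands in part. The plain meaning still covers both follow-up and analysis, and nothing in the protocol says these patients are retained.

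Three stronger readings are tempting, and the protocol does not support them:
- That the sickest or most distressed controls were in fact removed. No count or description is given, and the direction is open.
- That the Preliminary screening step is a second route of exclusion. It checks "to ensure that all the enrolled patients meet the eligibility inclusion and exclusion criteria" and that consent was given, in both arms, and states no removal.
- That the overlap between the EDSS and PDDS inclusion and exclusion wording adds to the problem. It is a separate eligibility matter, neither arm-specific nor triggered by allocation.

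**Conclusion.** The point holds for family-physician referrals. The stated rule excludes randomised patients from the control arm alone, after allocation is known and on perceived need. Confidence in that sequence is high because it is written twice. The effect is a loss of protection by randomisation, not a demonstrated imbalance.

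The bias may lie anywhere from near zero to about 0.66 points, or 44% of the 1.5-point target. The upper end needs 20% of all controls removed strictly from the top of the HADS distribution, an SD of about 3.77 and a correlation of 0.5. The affected share, the exclusion rate and the direction are all unreported, so no single figure should be quoted as the expected bias. The matter deserves correction because it touches the primary comparison and the remedy is cheap.

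**What to change.** Replace the exclusion sentences under Recruitment and under Control arm. State that outside referral, as the document already allows, does not end study participation, and that every randomised participant is followed where possible and analysed in the allocated arm. Patient access to outside care is unchanged.

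Trial status reports that recruitment and the last 6-month visit are complete, with final quality assurance and analysis still to come. What can be done before that analysis:

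- include any HADS data held for controls who left by this route, in the control arm;
- report the number of such exits and the reasons, by arm and by recruitment route;
- define the outside referral as an intercurrent event and say how the primary analysis handles it;
- add a sensitivity analysis for those without data, over a range of assumed outcomes.

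Recovery may be partial, because Table 1 places the baseline questionnaires after allocation and some of these patients may have returned no form. That makes the count itself important. Asking physicians about urgency before randomisation would prevent the problem, but can serve only future use of the design.

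The cost is protocol and analysis-plan wording plus a small amount of data retrieval. The sample size does not change. The one downside is that some analysed controls will have had other specialised care, which slightly dilutes the contrast.
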